### Sample size

The CATCH trial, which employed similar incentive schemes as the standard arm of the current trial, reported 41.1% abstinence at 12-month follow-up in the intervention arm versus 26.4% among participants who only attended the training sessions.^13^ The PERSIST trial will be embedded in healthcare institutions, many of which are currently implementing smoke-free policies, which is expected to be an extra external motivator for cessation. As such the validated abstinence percentages are expected to be slightly higher than in the CATCH trial, that is, 45% and 30%, respectively. We expect that personalisation of the incentives will further increase effectiveness to approximately 50%. In order to detect this difference in validated sustained abstinence (ie, 50% vs 30%) with a power of 0.8 and an alpha of 0.05 and using 1:1 randomisation, a total of at least 186 participants are needed. Taking into account a 15% loss to follow-up due to unexpected employee turnover,^11 24^ 220 participants are required. Further taking into account the potential maximum deviation from a 1:1 allocation ratio which may arise due to the stratified block randomisation procedure used, the minimum sample size required will increase in proportion to the number of different hospitals included in the trial. As the trial aims to estimate the effect of personalised incentives compared with no incentives and not to estimate the effect of each individual scheme, skewed allocation among the schemes is not an issue and is therefore not accounted for in the required sample size.

### Recruitment

Recruitment takes place at participating healthcare institutions, starting with Erasmus MC. Potential participants are informed about the group-based smoking cessation training sessions through internal websites, flyers, information sessions provided by SineFuma or by referral through their company doctor. Potential participants receive a letter explaining the different incentive schemes and the research procedures. On enrolment, informed consent is required.

### Allocation

Within participating institutions, participants will be individually randomised 1:1 to either the control or intervention arm. Permuted block randomisation with varying block sizes of four and six is used. There are two stratification factors: participating institution and readiness-to-quit (preparation or contemplation stage). A computer-generated allocation sequence was provided by ALEA randomisation service, in collaboration with the Erasmus MC Clinical Trial Centre. The block sizes will not be disclosed so as to ensure allocation concealment. ALEA will not release the randomisation result until the patient has been recruited into the trial and all baseline questionnaires have been completed. Participants are informed about their allocation by email. Inherent to the intervention and study design, participants and outcome assessors will not be blinded to allocation. Group session trainers will be blinded to allocation and data will be anonymised before analysis.

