### Trial design

The PERSIST trial is a randomised controlled non-blinded trial with two parallel arms.

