### Interventions

Eligible participants are individually randomised 1:1 into a control arm, receiving no incentives, and an intervention arm, receiving personalised incentives. See figure 1 for a flowchart. Both arms participate in a group-based smoking cessation training provided by SineFuma, a company specialised in supporting smoking cessation (www.rookvrijookjij.nl). Groups consist of 8–16 participants and the training consists of seven sessions of approximately 90 min duration held over a period of 8 weeks. Participants in the intervention and control arms participate in the same training sessions for logistical reasons. Group-based training sessions will start as soon as at least eight people have signed up to avoid participants lose motivation due to long waiting times.

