### Collection methods

As described in the Outcomes section, self-reported abstinence will be validated using expired air CO concentration readings obtained via a handheld monitor. Participants will be invited to complete web-based questionnaires assessing self-reported quality of life (EurQol Five Dimensions Health Questionnaire),^25^ smoking abstinence self-efficacy (Smoking Abstinence Self-efficacy Questionnaire),^26^ perceived stress (Perceived Stress Scale)^27^ and self-reported smoking abstinence (point prevalence and continuous abstinence)^23^ at each time point during follow-up. At baseline, the following items will be collected: educational level following the International Standard Classification of Education (ISCED;^28^ 0 (early childhood education) to 8 (doctoral or equivalent level)), individual gross monthly income (<€1500, €1500–1900, €1900–2600, >€2600), age, body mass index, gender and smoking behaviour (pack years, history of quit attempts and smoking history). In order to provide a personalised advise, the following questionnaires are also taken at baseline: nicotine dependency (Fagerström Scale),^19^ readiness-to-quit (Prochaska Stages of Change)^20^ and present bias (Kirby Discontinuity Scale).^21 29^ See table 2 for a schematic overview of data collection during the trial.

**Table 2 T2:** Schematic overview of data collection during the trial

Questionnaire	Baseline	t=0 month	t=3 months	t=6 months	t=12 months*	t=15 months
Demographic variables	X					
Fagerström Scale	X					
Prochaska Stage of Change	X					
Kirby Discontinuity Scale	X					
Willingness to pay a deposit	X					
EQ-5DF†	X	X	X	X	X	X
SASEQ‡	X	X	X	X	X	X
Perceived Stress Scale	X	X	X	X	X	X
Self-reported abstinence§	X	X	X	X	X	X
Evaluation training sessions		X				
Evaluation PERSIST						X

*t = 12 months is the primary endpoint.

†EurQol Five Dimensions Health Questionnaire.

‡Smoking Abstinence Self-efficacy Questionnaire.

§The self-reported abstinence questionnaire is adjusted to each corresponding time moment, for example, at t =3 the maximum period not smoked is 3 months and so on.

PERSIST, Personalised Incentives for Supporting Tobacco Cessation.

Participants will be sent reminders after 5 days for uncompleted questionnaires. A follow-up reminder will be sent 2 days later. If there are still open items, participants will be contacted by telephone 2 days after the last reminder and a follow-up phone call will be made another 2 days later.

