### Statistical methods

The primary analysis compares continuous smoking abstinence rates at 12 months after the group-based training session in the intervention arm against the control arm, following an intention-to-treat analysis. In secondary analyses, continuous smoking abstinence at 15 months is assessed to see if abstinence is sustained after the incentives stopped. All randomised participants will be included in the final analysis, those lost to follow-up will be classified as smoking except for an unavoidable loss to follow-up (eg, untraceable contact information or death, following the RS12).^23^ Generalised linear models with a logit link function will be used to assess the difference in the primary outcome between control and intervention arms at t=12 months and to account for clustering between hospitals.

Additionally, subgroup analyses will be performed to identify possible subgroup-specific effects of the intervention. Planned subgroup analyses are based on:

Readiness-to-quit. Preparation stage versus contemplation stage.^10 20^Degree of tobacco dependence. Fagerström score below 5 versus Fagerström score of 5 or higher.^19^Present bias. Delayed versus present reward preference. Delayed reward preference=more than 50% larger delayed reward is chosen or present reward preference=less than 50% larger delayed reward is chosen.^21 22^Income. Based on gross monthly income in €. Low income=below 1500 versus moderate/high income=above 1500.^30^Educational level. Based on the ISCED.^28^ Lower educated=ISCED 0–4 versus higher educated=ISCED 5–8.

Subgroup analysis is not included in the power analysis and therefore exploratory. For missing data on subgroup information, multiple imputations will be performed.

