### Strengths and limitations

The PERSIST trial is unique in its approach to personalising incentives to promote smoking cessation. Strong links between personal characteristics and effectiveness of incentives to promote smoking cessation have been demonstrated previously, however, to our knowledge, the effectiveness of personalised incentives has not been studied before.^14^ Another unique element of the PERSIST trial is that participants receive personalised advice for an incentive scheme, based on personal characteristics, yet are free to deviate from the advised scheme. Voluntary choice with a personalised default is a common tool in behavioural economics to nudge people towards the scheme that is plausibly in their best interest.^31^ This feature is scientifically innovative in the context of smoking cessation programmes and importantly lets the treated individuals choose the scheme they will be enrolled.

By focusing on supporting smoking cessation among hospital employees, the PERSIST trial is executed in a highly relevant setting, as in light of the National Prevention Agreement, all university hospitals have to be smoke free by 2020 and all general hospitals by 2025.^32^ Finally, the PERSIST trial progresses from previous studies by extending follow-up beyond the last time point when incentives are provided to investigate if participants remain abstinent when incentives are no longer provided.

A limitation of the PERSIST trial is that participants from the intervention and control arm attend the same cessation support training sessions due to practical reasons, as slow inclusion rates otherwise would have caused long waiting periods between signing up and starting the training. Participants in the control arm might perceive this negatively and potentially drop out, causing attrition bias. Another consequence could be spill-over effects^33^; sharing of vouchers between control and intervention arm, leading to a double underestimation of treatment effectiveness. To avoid this, participants are informed about their status as early as possible to make sure they have time to accept their status. A third arm consisting of non-personalised incentives could have provided additional potentially valuable information on the effectiveness of personalised incentives versus incentives provided according to a fixed scheme. However, this option would have required an unfeasibly large sample size.

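### Unblinded outcome assessment is called inherent to the design, but that is true only of participants; loss classification could be masked to arm, and trainer blinding is asserted without a described safeguard

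*Protocol article*

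**What the plan says.** All references are to the protocol article.

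- **Trial design:** "The PERSIST trial is a randomised controlled non-blinded trial with two parallel arms".
- **Allocation:** "Inherent to the intervention and study design, participants and outcome assessors will not be blinded to allocation". The next sentence adds: "Group session trainers will be blinded to allocation and data will be anonymised before analysis". The section also says: "Participants are informed about their allocation by email".
- **Interventions:** "Participants in the intervention and control arms participate in the same training sessions for logistical reasons".
- **Strengths and limitations:** "participants are informed about their status as early as possible to make sure they have time to accept their status".
- **Outcomes:** abstinence is self-reported and then checked by exhaled CO below 10 ppm. If the two disagree, the CO reading prevails.
- **Collection methods:** self-report is entered by web questionnaire. Open questionnaires trigger a reminder after 5 days and another 2 days later. Then "participants will be contacted by telephone 2 days after the last reminder", with a second call 2 days after that. No step depends on arm.
- **Statistical methods:** all randomised participants enter the analysis, and "those lost to follow-up will be classified as smoking except for an unavoidable loss to follow-up". Two examples of such a loss are given: death, and contact details that cannot be traced.

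**The concern.** The reason given for leaving assessors unblinded does not apply to them. Participants must know whether they can earn vouchers. The person who records a CO value, or who decides how a missing outcome is coded, need not.

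What is at stake is mostly the handling of missing outcomes, not the reading itself. A lost participant counts as smoking unless the loss is judged unavoidable. Deciding that a person is untraceable depends partly on how hard staff looked. The Sample size section attributes the expected 15% loss to employee turnover, and recruitment runs through the employer, so people who have left their job could plausibly raise this question. If the classifier knows the arm, the exception could be applied unevenly, even without intent.

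The trainer statement is a separate matter. If it is carried into the trial report, readers will credit the trial with protection against unequal coaching that it probably did not have.

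**Working it through.** **1. Is assessor unblinding inherent?** The Incentives section says the arms differ only in the provision of incentives, and these follow a validated abstinence result. The order is therefore result first, payment second. No described step needs the arm to be known before the result is stored. At 15 months no incentive is paid under any scheme, yet the statement about assessors makes no exception for that visit. The justification therefore covers participants only.

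**2. Does anonymising the data close the gap?** No. Removing identity is not the same as removing the arm. It is also placed before analysis, whereas loss status may be settled earlier.

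**3. Where can knowledge of arm reach the primary endpoint?**
- CO value: a numeric cut-off that overrides self-report. Little room.
- Questionnaire reminders: a fixed schedule, the same in both arms. Little room, apart from how the telephone calls are carried out.
- Unavoidable-loss exception: room for judgement, and a direct effect on how the endpoint is coded.

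**4. The plan's own figures.** Inputs from the Sample size section: 50% against 30%, power 0.80, alpha 0.05 (taken as two-sided), 1:1. With pooled variance under the null,

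n per arm = [1.960·√(2·0.40·0.60) + 0.842·√(0.50·0.50 + 0.30·0.70)]² / 0.20² = 93,

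so 186 in total, as stated. Then 186/0.85 = 218.8, or 219, which agrees with the rounded 220 (110 per arm). Fifteen per cent of 110 is 16.5, so about 16 losses per arm.

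**5. Size of the effect.** Assumptions, none of them from the document: 110 per arm; k losses exempted in one arm and none in the other; exempted cases removed from the denominator. The article says all randomised participants are analysed, so another handling of exempted cases would give other figures. The test is the pooled two-proportion z-test.

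*No true effect, 33/110 in each arm, k exempted in the intervention arm:*

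| k | Intervention | Spurious difference |
|---|---|---|
| 4 | 33/106 = 31.1% | 1.1 points |
| 8 | 33/102 = 32.4% | 2.4 points |
| 12 | 33/98 = 33.7% | 3.7 points |
| 16 | 33/94 = 35.1% | 5.1 points (p = 0.44) |

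*Borderline result, 46/110 against 33/110:*
- k = 0: difference 41.8% − 30.0% = 11.8 points; pooled p̂ = 79/220 = 0.359; SE = √[0.359·0.641·(2/110)] = 0.0647; z = 1.83; p = 0.068.
- k = 4: 46/106 = 43.4%, difference 13.4 points; pooled p̂ = 79/216 = 0.366; SE = √[0.366·0.634·(1/106 + 1/110)] = 0.0656; z = 2.04; p = 0.041.
- k = 8: p = 0.023.

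*Planned effect, 55/110 against 33/110:* p = 0.0025. If all 16 control losses and no intervention losses are exempted, the difference falls to 50.0% − 33/94 = 14.9 points and p = 0.032. The conclusion stands.

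**6. Trainer blinding.** Participants learn their arm by email, as early as possible. Both arms then sit together in groups of 8 to 16 for seven sessions of about 90 minutes. The article itself raises possible resentment among controls and possible sharing of vouchers across arms. No request that participants keep their arm to themselves is described. Disclosure in front of the trainer is therefore likely.

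**The case against.** The strongest reply is that this is a condensed article about a trial openly labelled non-blinded, with a biochemical endpoint, and that several stronger inferences go beyond the text. Most of that is right:

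- A reader might infer that staff who know the arm decide who is chased. The document does not support this for questionnaires, where the schedule is fixed and neutral to arm.
- A reader might infer that unblinded staff are named as the judges of unavoidable loss. No decider is named. The full protocol or analysis plan may name one, and silence on that is not a fault of the article. The two examples given are also largely factual.
- A reader might infer that trainer blinding is impossible, or that the first voucher reveals the arm during coaching. Shared sessions make disclosure likely, not certain, and the first voucher comes only after the last session.
- A reader might link trainer unblinding to bias in the endpoint. Trainers are not named as outcome assessors, so the link is not there.

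A further fair point is that participants can reveal their arm to whoever telephones them or takes their breath reading, just as they can to a trainer. Masking of those contacts would be partial. That does not apply to classifying losses and final status from a coded listing, which involves no contact with participants.

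What remains is what the article itself states: a justification that does not fit assessors, and a claim of trainer blinding with no described support.

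**Conclusion.** The point holds in a limited form. Calling unblinded outcome assessment inherent is correct for participants and unsupported for those who classify the outcome. The exposed step is the unavoidable-loss exception. Its likely effect is small: a few exemptions in one arm shift the difference by about 1 to 2 points, against a standard error of about 6.5 points. Under no effect, even the extreme of 16 one-sided exemptions gives 5.1 points and no significant result. At the planned effect the conclusion survives. Only a result near the boundary is at risk, as in the move from p = 0.068 to 0.041. All these figures rest on assumed one-sided counts and on exempted cases leaving the denominator; they are illustrations, not estimates.

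The trainer statement should be corrected for accuracy of reporting. It bears on the equality of coaching and does not show bias in how the endpoint is assessed.

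One limit stays whatever is changed: CO shows only recent smoking, so continuous abstinence still relies partly on self-report by participants who know their arm.

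**What to change.** 1. **Allocation, assessors.** Limit the sentence on what is inherent to participants. State that existing staff classify unavoidable losses, and the final abstinence status, from coded listings without arm, before allocation is merged. Where feasible, use worklists without arm for CO readings and telephone calls, and release vouchers after the result has been stored.
2. **Allocation, trainers.** Replace the statement that trainers will be blinded with one that they are not told allocation. Ask participants not to disclose their arm in sessions. Do not report trainers as blinded.

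The cost is protocol wording and a change in the order of work, with no extra staff and no change in sample size. The downsides are slightly later voucher release and incomplete masking of readings and calls, because some participants will reveal their arm.

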### Collection methods

As described in the Outcomes section, self-reported abstinence will be validated using expired air CO concentration readings obtained via a handheld monitor. Participants will be invited to complete web-based questionnaires assessing self-reported quality of life (EurQol Five Dimensions Health Questionnaire),^25^ smoking abstinence self-efficacy (Smoking Abstinence Self-efficacy Questionnaire),^26^ perceived stress (Perceived Stress Scale)^27^ and self-reported smoking abstinence (point prevalence and continuous abstinence)^23^ at each time point during follow-up. At baseline, the following items will be collected: educational level following the International Standard Classification of Education (ISCED;^28^ 0 (early childhood education) to 8 (doctoral or equivalent level)), individual gross monthly income (<€1500, €1500–1900, €1900–2600, >€2600), age, body mass index, gender and smoking behaviour (pack years, history of quit attempts and smoking history). In order to provide a personalised advise, the following questionnaires are also taken at baseline: nicotine dependency (Fagerström Scale),^19^ readiness-to-quit (Prochaska Stages of Change)^20^ and present bias (Kirby Discontinuity Scale).^21 29^ See table 2 for a schematic overview of data collection during the trial.

**Table 2 T2:** Schematic overview of data collection during the trial

Questionnaire	Baseline	t=0 month	t=3 months	t=6 months	t=12 months*	t=15 months
Demographic variables	X					
Fagerström Scale	X					
Prochaska Stage of Change	X					
Kirby Discontinuity Scale	X					
Willingness to pay a deposit	X					
EQ-5DF†	X	X	X	X	X	X
SASEQ‡	X	X	X	X	X	X
Perceived Stress Scale	X	X	X	X	X	X
Self-reported abstinence§	X	X	X	X	X	X
Evaluation training sessions		X				
Evaluation PERSIST						X

*t = 12 months is the primary endpoint.

†EurQol Five Dimensions Health Questionnaire.

‡Smoking Abstinence Self-efficacy Questionnaire.

§The self-reported abstinence questionnaire is adjusted to each corresponding time moment, for example, at t =3 the maximum period not smoked is 3 months and so on.

PERSIST, Personalised Incentives for Supporting Tobacco Cessation.

Participants will be sent reminders after 5 days for uncompleted questionnaires. A follow-up reminder will be sent 2 days later. If there are still open items, participants will be contacted by telephone 2 days after the last reminder and a follow-up phone call will be made another 2 days later.

### Data management

Informed consent will be provided digitally through LimeSurvey (LimeSurvey GmbH, Hamburg, Germany). All trial data will be entered electronically using GemsTracker (GemsTracker, Erasmus MC and *Equipe Zorgbedrijven*, Rotterdam, The Netherlands). Data are handled confidentially and stored anonymously, where data need to be linked to an individual subject (eg, linking longitudinal data), a subject identification code will be used. The code will not be based on patient initials and date of birth to preserve anonymity. The key to the code will be safeguarded by the investigator and kept separate from data files. All of the study essential documents will be retained and archived for 15 years after completion of the study. They will be stored securely and adequately protected from damage.

### Statistical methods

The primary analysis compares continuous smoking abstinence rates at 12 months after the group-based training session in the intervention arm against the control arm, following an intention-to-treat analysis. In secondary analyses, continuous smoking abstinence at 15 months is assessed to see if abstinence is sustained after the incentives stopped. All randomised participants will be included in the final analysis, those lost to follow-up will be classified as smoking except for an unavoidable loss to follow-up (eg, untraceable contact information or death, following the RS12).^23^ Generalised linear models with a logit link function will be used to assess the difference in the primary outcome between control and intervention arms at t=12 months and to account for clustering between hospitals.

Additionally, subgroup analyses will be performed to identify possible subgroup-specific effects of the intervention. Planned subgroup analyses are based on:

Readiness-to-quit. Preparation stage versus contemplation stage.^10 20^Degree of tobacco dependence. Fagerström score below 5 versus Fagerström score of 5 or higher.^19^Present bias. Delayed versus present reward preference. Delayed reward preference=more than 50% larger delayed reward is chosen or present reward preference=less than 50% larger delayed reward is chosen.^21 22^Income. Based on gross monthly income in €. Low income=below 1500 versus moderate/high income=above 1500.^30^Educational level. Based on the ISCED.^28^ Lower educated=ISCED 0–4 versus higher educated=ISCED 5–8.

Subgroup analysis is not included in the power analysis and therefore exploratory. For missing data on subgroup information, multiple imputations will be performed.

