Degree of tobacco dependence. Based on the Fagerström Test for Nicotine Dependence.^19^ Fagerström score below 5=no/low nicotine dependence or Fagerström score of 5 or higher=nicotine dependent.Readiness-to-quit. Based on Prochaska Stage of Change.^20^ Preparation stage (readiness to quit within the next 30 days) or (pre)contemplation stage (ready to quit within the next 6 months or not ready to quit at all).^10 20^Present bias. Measured by temporal discounting magnitude based on the Kirby Scale.^21^ Temporal discounting refers to the phenomenon where future rewards are perceived as being worth less than an immediate reward.^21^ Based on a 27-item monetary choice questionnaire, those choosing more than 50% of the times the larger delayed rewards are classified as having delayed reward preference and those choosing less than 50% of the times the larger delayed rewards are classified as having present reward preference.^21 22^Willingness to pay a deposit, yes or no.

The first three factors have been associated with the effectiveness of smoking cessation interventions and with reaching sustained abstinence in reward-based programmes.^14^ The fourth factor is used as an indicator of acceptability of the deposit-based scheme, as deposit schemes are expected to be not only the most effective but also the least popular. The four factors are dichotomised into ‘positive’ or ‘negative’ values in order to advise participants. Positive values are associated with higher quit percentages, that is, being in a preparation stage, having low nicotine dependence and having a delayed reward preference. Negative values are associated with lower quit percentages, that is, being in a (pre)contemplation stage, being nicotine dependent and having an immediate reward preference.

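### The primary model as described leaves out nicotine dependence and reward preference, which the protocol calls predictive and collects before allocation; adding them would be a modest efficiency gain, not the correction of an error

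*Protocol article*

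**What the plan says.** The Statistical methods section fixes the primary analysis as an intention-to-treat comparison of continuous abstinence at 12 months: "Generalised linear models with a logit link function will be used to assess the difference in the primary outcome between control and intervention arms". It adds that the model accounts for clustering between hospitals. It names no baseline covariate. Further down, the same section lists readiness-to-quit, Fagerström score and reward preference as subgroup variables, and calls the subgroup analyses exploratory.

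The Incentives section says of these same variables: "Positive values are associated with higher quit percentages, that is, being in a preparation stage, having low nicotine dependence and having a delayed reward preference". The advice on incentive schemes (Table 1) is built on that statement.

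The Allocation section stratifies by institution and readiness-to-quit only. It also says: "ALEA will not release the randomisation result until the patient has been recruited into the trial and all baseline questionnaires have been completed". The Collection methods section and Table 2 list the Fagerström and Kirby scales among the baseline questionnaires.

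The Sample size section states that "a total of at least 186 participants are needed", "with a power of 0.8 and an alpha of 0.05 and using 1:1 randomisation", for 50% against 30% abstinence. After a 15% allowance for loss, "220 participants are required".

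**The concern.** The protocol relies on dependence and reward preference enough to let them steer the scheme advice, but as written it does not use them in the primary comparison. Neither is a stratification factor, so chance alone governs their balance. With 110 per arm and an assumed prevalence of 50%, the 95% limits for a chance difference in the share who are nicotine dependent are ±1.96 × √(2 × 0.25/110) = ±13 percentage points.

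What is at stake is precision. Adjusting for a baseline variable that predicts the outcome usually sharpens the test of the arm effect. The data should be nearly complete, because allocation waits for the questionnaires. The trial is sized for 80% power, with an increase for loss and a further increase for uneven allocation across hospitals, so a few points of power are worth having. Participants and outcome assessors are not blinded, so covariates chosen after results are seen would be open to challenge. The choice is credible only if made beforehand.

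**Working it through.** **Inputs.** From the Sample size section: 30% and 50% abstinence, alpha 0.05 (two-sided reproduces the figure), power 0.80, 1:1 allocation, 186 evaluable, 15% loss, 220 in total. The documents give no prognostic strength, so every odds ratio below is an assumption.

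**Step 1: the plan's own figure.** Pooled-variance formula for two proportions, without continuity correction:

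n per arm = [1.960 × √(2 × 0.40 × 0.60) + 0.842 × √(0.30 × 0.70 + 0.50 × 0.50)]² / 0.20²
= [1.358 + 0.571]² / 0.04 = 93, so 186 in total.

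Power at 186 is 80.0%. Loss: 186/0.85 = 218.8, so 219, against 220 stated. Both figures reproduce.

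**Step 2: power at the number analysed.** The Statistical methods section counts most losses as smoking, so close to 220 would be analysed.
- If 50% and 30% already count losses as smokers, power at 220 is 86.2%.
- If 15% loss dilutes the rates to 0.85 × 50% = 42.5% and 0.85 × 30% = 25.5%, power at 220 is 76.2%.

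**Step 3: logistic Wald test, continuous score.** Simulation at 186 with marginal rates of 30% and 50%. The score predicts equally in both arms, and two pure-noise covariates are also in the adjusted model.

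| Log odds ratio per SD | Arm only | Adjusted | Gain (points) |
|---|---|---|---|
| 0.4 | 79.5% | 81.2% | 1.7 |
| 0.6 | 79.3% | 82.8% | 3.5 |
| 0.8 | 80.1% | 84.5% | 4.4 |

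Gains are similar at 220 with the diluted rates. With a score of no prognostic value, a separate run (3,000 trials, score only) gave 79.9% unadjusted and 80.1% adjusted.

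**Step 4: the score predicts only in the incentive arm.** 6,000 trials at 186, score only:
- log odds ratio 0.4: 78.9% to 79.5%
- 0.6: 79.5% to 80.7%
- 0.8: 79.5% to 81.2%

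That is 0.6 to 1.7 points. Allowing for the noise covariates, about 1 point or none is a fair summary.

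**Step 5: two binary covariates added to readiness.** Dependence and reward preference, each 50% prevalent and independent; readiness has the same odds ratio and is already in the model. 6,000 trials at 186:
- odds ratio 1.5: 79.4% to 80.7% (gain 1.3)
- odds ratio 2: 81.2% to 83.7% (gain 2.5)
- odds ratio 3: 82.5% to 86.3% (gain 3.8)

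**Step 6: standardised risk difference, dependence and reward preference alone.** Let m₀ and m₁ be the abstinence probabilities in control and intervention, given the covariates. The unadjusted variance (times N) is V = 2 × (0.30 × 0.70 + 0.50 × 0.50) = 0.92. Adjustment removes Var(m₀ + m₁).

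For odds ratio 2, participants with 0, 1 or 2 favourable values (weights ¼, ½, ¼) have m₀ = 0.170, 0.290, 0.450 and m₁ = 0.333, 0.500, 0.667. The sums are 0.503, 0.790 and 1.117, with mean 0.80 and variance 0.047. The variance ratio is 1 − 0.047/0.92 = 0.949.

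Power at 186 = Φ(0.20/√(V/186) − 1.960), which is 81.2% at V = 0.92 and 83.1% at 0.949 × 0.92.

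| Odds ratio | Variance ratio | Power at 186 (unadjusted 81.2%) | Equivalent participants of 220 |
|---|---|---|---|
| 1.5 | 0.982 | 81.9% | 220 × 0.018 ≈ 4 |
| 2 | 0.949 | 83.1% | 220 × 0.051 ≈ 11 |
| 3 | 0.884 | 85.6% | 220 × 0.116 ≈ 26 |

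At 220 with the diluted rates, the same calculation goes from 77.2% to 77.9%, 79.2% and 81.8%.

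**The case against.** The strongest objection is one of scope. A covariate list is commonly left to the statistical analysis plan, which is not shown. The article names no covariates but does not exclude them or call the analysis unadjusted. This stands as a caveat: if the analysis plan already names them, the sponsor need only confirm it. It does not remove the point, because the article describes the model and gives these variables a role only in subgroups.

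Second, a reader might infer that the unadjusted test is biased, or that the trial misses its stated power. The documents do not support either. Randomisation makes the comparison valid without covariates, and Step 1 reproduces 80% at 186.

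Third, a reader might take these variables to be strong predictors. The Incentives section states association, not strength, and part of its support comes from reward-based programmes, which the control arm does not receive. That is why Step 4 belongs in the range.

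Fourth, baseline abstinence self-efficacy is also collected and might look like a natural covariate. No section says that it predicts quitting, so these documents give no basis for adding it. Readiness-to-quit, by contrast, is named as prognostic on the same footing and is a stratification factor, so it belongs in the model.

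Last, the gain has a price in interpretation: in a logit model the adjusted odds ratio is conditional on the covariates. A standardised risk difference deals with this.

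**Conclusion.** The point holds as an efficiency improvement. The primary model as described does not use baseline variables that the protocol itself links to quitting and has in hand before allocation.

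The expected gain is modest. It is about 1 to 5 power points if a score has a log odds ratio of 0.4 to 0.8 per standard deviation in both arms, and about 1 point or none if it predicts only in the incentive arm. No material power is lost if it predicts nothing. These sizes rest on assumed prognostic strength, and those in Steps 5 and 6 also on assumed prevalence and independence. The planned test remains valid and has its stated power on the plan's own assumptions.

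**What to change.** Prespecify three baseline covariates in the primary logit model, beside arm and hospital: the Fagerström score and the Kirby proportion of larger delayed choices, both continuous, and readiness-to-quit as stratified. Leave self-efficacy out. If the statistical analysis plan already names these covariates, a sentence confirming it is enough.

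State the effect measure. Report the conditional odds ratio together with a standardised (marginal) risk difference, so that the result stays comparable with the planned 50% against 30%.

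The Statistical methods section already plans multiple imputation for missing subgroup information. Apply imputation also to any rare missing covariate value, so that no randomised participant leaves the primary analysis for lack of a baseline score.

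The cost is wording, fixed before outcome data are examined. No new data collection or change in sample size is needed.
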